## Abstract

Type 2 diabetes mellitus is a disease in which insulin action is impaired, and an acute bout of strength exercise can improve insulin sensitivity. Current guidelines for strength exercise prescription suggest that 8 to 30 sets could be performed, although it is not known how variations in exercise volume impact insulin sensitivity. Additionally, this means an almost 4-fold difference in time commitment, which might directly impact an individual’s motivation and perceived capacity to exercise. This study will assess the acute effects of high- and low-volume strength exercise sessions on insulin sensitivity. After being thoroughly familiarized, 14 obese individuals of both sexes (>40 year old) will undergo 3 random experimental sessions, with a minimum 4-day washout period between them: a high-volume session (7 exercises, 3 sets per exercise, 21 total sets); a low-volume session (7 exercises, 1 set per exercise, 7 total sets); and a control session, where no exercise will be performed. Psychological assessments (feeling, enjoyment, and self-efficacy) will be performed after the sessions. All sessions will be held at night, and the next morning, an oral glucose tolerance test will be performed in a local laboratory, from which indexes of insulin sensitivity will be derived. We believe this study will aid in strength exercise prescription for individuals who claim not to have time to exercise or who perceive high-volume strength exercise intimidating to adhere to. This trial was prospectively registered (ReBEC #RBR-3vj5dc5 https://ensaiosclinicos.gov.br/rg/RBR-3vj5dc5).

## Introduction

Diabetes Mellitus (DM) is a condition in which blood glucose levels remain high in the face of insufficient insulin production and/or reduced insulin sensitivity [1]. Hyperglycemia can lead to severe and life-threatening disorders, such as cardiovascular disease, nerve and kidney damage, amputation of limbs, vision loss and even blindness [1]. The number of people affected by DM has grown exponentially, and by 2017, this disease was the ninth leading cause of death in the entire world [2]. In 2021 it was responsible for 12.2% of global deaths in people aged 20–79 [1]. DM is related to high financial costs [3], and in Brazil, the total expenditure on DM in 2014 was more than R$ 26 billion (~US$ 5.5 bi) [4]. Approximately 90–95% of DM cases are type 2 (DM2) [5], which is related to the impairment of insulin sensitivity induced by obesity [6].

The beneficial effects of strength training on insulin sensitivity have been increasingly recognized. Interestingly, though, it has been reported that the training-induced improved insulin sensitivity may be lost after as few as 4–6 days following the last training session [7–9], suggesting the positive effects of exercise on glycemic control can be largely attributed to the acute improvements observed in the hours-days after each exercise bout [10]. Notably, several studies point to the beneficial effects of a single acute bout of strength exercise on improving insulin sensitivity [11], and it has been reported that strength exercise sessions increase insulin sensitivity for up to 48 hours [10]. Thus, understanding strength exercise prescriptions that elicits acute improvements in insulin action is of great clinical value.

Studies carried out over the last 30 years have shown that a strength exercise session is capable of improving insulin sensitivity. For instance, Koopman et al [12] reported that a strength exercise session (25 sets, 10 repetitions [reps], 75% 1 rep maximum [RM]) improved insulin sensitivity, measured by an insulin tolerance test, in healthy young men. Similar results were observed by Tong et al [13] who evaluated the effects a strength exercise session (9 sets, 10 reps, 75% 1RM) in nondiabetic men and showed a decreased glucose and insulin area under the curve (AUC) in response to an oral glucose tolerance test (OGTT). Andersen and Høstmark [14] observed in strength-trained men lower glycemic response to a meal test 14 hours after a session of strength exercises (21 sets, 10 reps, 65% 1RM), and more recently, Monroe et al [15] also studied trained men and reported improved capillary glucose levels after moderate- and high-load, volume-matched, strength exercise sessions (35 sets, 3 reps, at 90% 1RM and 15 sets, 9 reps, 70% 1RM). The acute benefits of strength exercise on insulin sensitivity have also been investigated in older and obese subjects, as well as patients living with prediabetes and DM2. For example, Bittel et al [16] demonstrated that a strength exercise session (21 sets, 10–12 reps, 80% 1RM) increased insulin sensitivity in response to a mixed meal in obese men, while Fluckey et al [17] evaluated young individuals and older patients living with and without DM2 in response to an acute strength exercise session (21 sets, 10 reps, 50, 75 and 100% of 75% 1RM) and observed a smaller insulin AUC in both young individuals and in DM2 patients. Van Dijk et al [10] studied individuals living with prediabetes, and with DM2 in response to a session of strength exercise (16 sets, 10 reps, 40–75% 1RM) and reported decreased average concentrations of glucose, and prevalence of hyperglycemia over 24 hours.

On the other hand, some studies did not demonstrate positive effects of a strength exercise session on insulin sensitivity. In apparently healthy individuals, one session of strength exercises (15 sets, 10 reps, 45–70% 1RM) led to unfavorable and clinically significant increases in insulin response [18], and in sedentary postmenopausal women no improvements were observed in insulin sensitivity, glycemia, and C-peptide response (an index of insulin release from beta cells) after a bout of strength exercise (21 sets, 10 reps, 50–100% 10RM) [19]. In strength trained men, Luebbers et al [20] reported no change in insulin sensitivity after high- (24 sets, 8 reps, 85% 10RM) or low-load (24 sets, 15 reps, 45% 10RM) sessions of strength exercise. Furthermore, Malin et al [21] studied non-diabetic women with normal fat percentage (<35%) and with high fat percentage (>40%) and observed no change in insulin sensitivity after a bout of strength exercise (30 sets, 10–12 reps, 60% 1RM). Finally, no beneficial effects of a session of strength exercises (15 sets, 10 reps, 45–70% 1RM) on insulin sensitivity were observed individuals living with DM2 [22] or on glycemic control in a combined sample of individuals living with prediabetics and DM2 (18 sets, 10 reps, 65% 1RM) [22].

Clearly, the literature pertaining to the acute effects of a strength exercise session on insulin sensitivity is conflicting. However, it is possible to identify characteristics within exercise prescription variables that may explain the differing results. In a narrative literature review, Brown et al [23] identified 14 studies that evaluated the effects of a strength exercise session on insulin sensitivity. It was observed that concentric muscular failure (characterized as the inability to continue the set due to failure in the concentric moment of the movement of a given rep) is fundamental for observing improvements in glycemia and insulin sensitivity, since this certifies maximum (or close to maximum) effort during the sets. Moreover, it was noted that studies with positive results prescribed higher number of sets, which leads to higher exercise volume. In fact, a recent systematic review and meta-analysis reported that strength exercise sessions with 21 sets or more showed a greater improvement in glycemic control compared to sessions with fewer than 21 sets [24]. Nonetheless, current guidelines suggest that for improving glucose metabolism a strength exercise session could be composed of 8 to 10 exercises and 1 to 3 sets for each exercise [25], which translates into a wide range of total exercise volume and, by default, time commitment.

Studies that have assessed the acute effects of strength exercise volume on insulin sensitivity are scarce [11]. Reed et al [26] studied 1 or 3 sets (10 exercises, 10 reps, 65% 1 RM), performed in a circuit style program, in normoglycemic women, and found a significant improvement in insulin sensitivity only after the session with higher volume. Unfortunately, the prescription of strength exercise in circuit style prevents inferences for traditional strength exercise. Black et al [27] evaluated 8 exercises performed with 1 or 4 sets, either at 65% 1RM (12–15 reps) or 85% 1RM (6 to 8 reps). The authors observed improvements in insulin resistance in all protocols; but, protocols with single sets showed less effect. However, in that study, the degree of effort in each set was not reported and arguably higher in the high-volume conditions, and as this parameter is suggested as a determinant in the improvement of insulin sensitivity [23], one cannot exclude the possibility this factor played a role in the results observed. Furthermore, Black et al [27] assessed insulin resistance by the homeostasis model assessment of insulin resistance (HOMA-IR), which is more limited than other methods, such as OGTT-derived indexes [28], and more closely reflects hepatic insulin resistance [29]. These few studies in the literature, as well as their limitations, show the need for more research on the effects of strength exercise volume on insulin sensitivity.

Another important point regarding the prescription of strength exercise are the factors that prevent people from regularly engaging in exercise training. When asked about non-adherence to an exercise protocol, the most frequent justification is lack of time [30]. In addition, low self-efficacy (self-perception of the inability to accomplish something) is also one of the reasons people do not exercise frequently [31]. Additionally, positive feelings experienced in response to exercise are important factors for long-term adherence to an exercise program [32, 33]. Therefore, investigating the effect of low- and high-volume strength exercise–which leads to low and high time commitment, respectively [34]–on insulin sensitivity can be beneficial to motivate people who claim not to have time to perform strength exercises and for those who feel that they are not able to or do not experience positive feelings when performing high volumes of strength exercise.

## Objective

### Primary objective

The primary objective will be to investigate the acute effects of high- and low-volume strength exercise sessions on insulin sensitivity indexes in obese adults.

### Secondary objective

Assess the acute effects of high- and low-volume strength exercise sessions on feeling, enjoyment, and self-efficacy in obese adults.

## Methods

### Ethics approval

This study was approved by the local institutional review board (the Research Ethics Committee of the Federal University of the Jequitinhonha and Mucuri Valleys—certificate number CAAE 63190422.0.0000.5108) and complies with the Declaration of Helsinki. The present study was prospectively registered in a clinical trial registry (ReBEC #RBR-3vj5dc5 https://ensaiosclinicos.gov.br/rg/RBR-3vj5dc5). Any modifications to the protocol will be submitted to the ethics committee, followed by an updating of the trial registry.

### Description of participants

Altered insulin sensitivity is associated with increased lipotoxicity, a consequence of increased body fat [35]. Thus, the inclusion criteria are obese individuals of both sexes, aged over 40 years, with central obesity (waist circumference > 102 cm in men and > 88 cm in women), with stable body mass (±3 kg) in the last 3 months and able to perform physical activity [36]. To confirm obesity and central obesity statuses of the participants, dual-energy X-ray absorptiometry will be used to assess fat percentage and visceral fat mass (see details below in **Anthropometric measurements**), and participants will be included only if both indexes are >90^th^ percentile for age and sex [37]. Exclusion criteria are individuals with signs, symptoms or presence of diabetes or any other metabolic disease, cardiovascular disease, cerebrovascular disease, kidney disease, respiratory disease, and osteoarticular disease [36]. In addition, those who report using any medication that may influence the expected results (including oral contraceptives [38]) and use of anabolic steroids or being pregnant will be excluded. Furthermore, participants who describe dietary supplement intake known to affect exercise performance, such as caffeine, beta-alanine, creatine, and sodium bicarbonate [39] will be excluded. Participants will be from the local community (Diamantina, MG–Brazil) and the project will be publicized through social media, posters at strategic points in the city, and word of mouth. After showing interest, participants will receive information by the researchers ([name] or [name]) about the objectives of the work, possible discomforts, risks and benefits before volunteering. After being thoroughly informed of the study’s risks and benefits, and before initiating participation, subjects will sign an "Informed Consent Form" (available upon request), previously approved by the local institutional review board. Participants will be reimbursed for expenses incurred due to the research and resulting from it. At any time if they suffer any damage, unarguably resulting from this research, they will be entitled to compensation, full and immediate assistance, free of charge for as long as necessary.

### Study type and design

This study will be a randomized controlled, crossover, 3-arm, clinical trial. The protocol description followed the SPIRIT [40] and the TIDieR [41] guidelines (Fig 1 and S1–S3 Tables). Participants will undergo a health history questionnaire, anthropometric measures which include height, body mass, waist circumference and body composition, a period of familiarization and strength assessment. At least 4 days after the strength tests, they will carry out 3 randomized experimental sessions, separated by at least 4 (but no more than 28) washout days, as it has been shown that the acute effect of exercise on improved insulin action lasts up to 2 days [42]. In case the sessions are scheduled 21 to 28 days apart, participants will be required to perform a familiarization session 2 weeks after the preceding (and 1 to 2 weeks before the following) experimental session to avoid defamiliarization. The interval between experimental sessions will be recorded and reported in the final manuscript, and discussed accordingly. To avoid the variation in insulin sensitivity across the menstrual cycle [43–49], in case premenopausal women are included in the sample, they will be assessed in the follicular phase (days 1–14) [9, 26, 50–52] of their menstrual cycle. Two of the experimental sessions will be performed with strength exercises: a high-volume session [3 sets per exercise–high volume]; a low-volume session [1 set per exercise–low volume]; and a control session: no exercise. In the exercise sessions, 7 exercises will be performed for the major muscle groups (1 –hex bar squat; 2 –bench press; 3 –leg press; 4 –lat pulldown; 5 –leg extension; 6 –shoulder press; 7 –leg curl; Fig 2), totaling 21 sets in the high-volume session and 7 sets in the low volume session [24]. The sessions will be held at night, between 8:00 pm and 9:00 pm. This time schedule for the sessions is ecologically valid, as exercise in the evening is commonly observed in fitness centers due to time constraints for exercising earlier during the day [13, 53], and it has been shown that night-time exercise does not affect sleep duration or quality [53]. The next morning between 7:00 am and 8:00 am (between 10 and 11 hours after the session), an OGTT will be performed in a local clinical laboratory. Participants will respond to scales of feeling, enjoyment, and self-efficacy after the exercise sessions. All sessions will be supervised by a certified fitness professional. The experimental design is illustrated in Fig 3.

**Fig 1 pone.0302480.g001:**
[figure not shown]
SPIRIT schedule of assessments at different time points. OGTT: oral glucose tolerance test; *Sessions order is randomized with >3-day washout period.

**Fig 2 pone.0302480.g002:**
[figure not shown]
Exercises that will be prescribed for the strength exercise sessions. 1. Hex bar squat, 2. Bench press, 3. Leg press, 4. Lat pulldown, 5. Leg extension, 6. Shoulder press, 7. Leg curl.

**Fig 3 pone.0302480.g003:**
[figure not shown]
Illustration of the experimental protocol timeline. BMI: body mass index; PACES: physical activity enjoyment scale; OGTT: oral glucose tolerance test; IS: insulin sensitivity.

Subjects’ participation will be discontinued in case of withdrawn consent, or in case the interval between sessions is higher than 28 days. We will report reasons for withdrawal and discuss the reasons qualitatively in the final manuscript. Adverse events related or nonrelated to the research protocol experienced by participants during study (e.g. skeletomuscular injury, having a cold, etc.) will be carefully recorded and reported in the final manuscript.

### Pre-participation screening

Participants will answer a health questionnaire based on the most recent recommendations of the American College of Sports Medicine [36] that will assess possible risks of performing the exercise protocol.

### Anthropometric measurements

Individuals will be submitted to the measurement of body mass and height on an analog scale, with a stadiometer attached, to calculate the BMI. Subsequently, the waist circumference of the participants will be measured. Then, the body composition will be evaluated by means of dual-energy X-ray absorptiometry (DXA, Lunar, iDXA Advanced). Participants will be accommodated in the device, following the manufacturer’s instructions for analysis of fat mass, fat-free mass, and visceral fat mass.

### Familiarization

A thorough familiarization period will be carried out in each of the 7 strength exercises (3 sets/exercise x 8 reps/set). On the first day, the participant will be instructed to lift a light load, in which performing 8 reps is considered “somewhat easy” or between “3” and “4” according to the OMNI-RES scale [54]. In the second session, a load considered “somewhat hard” or between “5” and “7” should be lifted. In the third session, the load will be considered “hard”, or between “7” and “9”. In the 4^th^ session, they should lift loads between “hard” and “extremely hard” or between “9” and “10”, mimicking the effort expected in the strength test itself. The interval between sets will be 120 seconds. After this, a fifth familiarization session will be performed to mimic the strength tests (see below in **Strength tests**). In all sessions, the correct form for each exercise (range of motion, duration of concentric:eccentric phases [~1:2 sec; aka tempo]) will be carefully observed, and corrections will be made. Furthermore, in every session, participants will be familiarized with the subjective measurements (feeling, enjoyment, and self-efficacy, see below). All sessions will be supervised by a certified fitness professional. The interval between familiarization days will be at least 48 but no more than 168 hours (2 to 7 days).

### Strength tests

At least 72 hours after the last familiarization session, participants will perform the 8-RM test on each of the 7 exercises. After an initial 5 minute warm-up walking on a treadmill (~3–4 km/h), and 1 set with low-load (12 reps, ~40–50% 1RM, ~3–4 OMNI), the participant will be instructed to perform 8 reps, and the load will be gradually increased with each set until the participant is able to perform only 8 reps (with full range of motion and tempo ~1:2 sec). The rest period between attempts will be between 120 and 180 seconds [55]. Because during the high- and low-volume experimental sessions participants will perform all seven exercises sequentially, and fatigue will likely accumulate as the sessions progresses, we decided to have their 8-RM tested in the same fashion, in order to mimic their anticipated effort. This means a true 8-RM might not be recorded, especially for exercises tested later in the strength test session. However, we believe this will not interfere with our study design and results interpretation, as exactly the same load will be prescribed for the exercise experimental sessions. All tests will be performed under the supervision of the same person, and the results will serve as a basis for prescribing exercise sessions.

### Random allocation

The order in which the experimental sessions will be held will be randomized with the aid of the website https://www.randomizer.org. The random orders generated by the program will be printed and inserted inside opaque, sequentially numbered envelopes, which will later be sealed by a research collaborator not directly involved in data collection. After completing the strength tests, the envelope will be opened, and the sequence of experimental sessions that will be followed will be revealed.

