### Statistics

#### Sample size

The sample size was calculated from the literature [10, 12, 16, 17, 19, 23, 26, 27, 77] using the G*Power program (Heinrich-Heine-Universität Düsseldorf, Germany, version 3.1.9.6), inserting the parameters for a one-way ANOVA, effect size of 0.6 probability of error type alpha of 0.05 and power (probability of error type 1 –beta) of 0.9. With these parameters, 14 individuals will be needed (actual power of 0.93). Due to the usual sample loss of 25–40%, we will initially recruit 20 participants. In order to promote participant retention, frequent text messages will be sent as reminders to follow the instructions, and to show up in the scheduled sessions. Also, in case the participant misses a session, all effort will be made to reschedule as long as it is within 28 days of the previous session. Dropout reason will be recorded and reported in the manuscript.

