Data will be expressed as the mean and standard deviation with a confidence interval of 95%. For the analysis of data normality, we will perform the Shapiro-Wilk test. For normally distributed data, analysis of variance will be used with one source of variation (experimental situation). If a significant main effect was observed, post hoc Tukey test was used. For non-parametric data, the Kruskal-Wallis test was used, or Friedman’s test, when necessary. Effect size was calculated and interpreted as follows: <0.2 = no effect, 0.2–0.49 = low effect, 0.5–0.79 = medium effect, and greater than 0.8 = large effect [81, 82]. The significance level will be 5%. The Prisma program (GraphPad Software, San Diego, CA-USA–version 8.4.0) will be used to analyze the results. The trial will be reported following the CONSORT guidelines [83, 84].

As stated above under **Blinding procedures**, the researcher responsible for data analysis (the statistician) will be blinded for group allocation. For that, a collaborator outside the research team will double enter data coded for allocation into a computer in separate spreadsheets so that the researcher responsible for data analysis can assess data without having access to information about the allocation. Allocation will only be revealed after statistics are run. In case there are doubts about data entry (missing values, or values outside the reference range), the researcher responsible for data analysis will contact the collaborator outside the research team responsible for double entry of the data to check accuracy. There will be no interim analysis.

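### The three-session crossover is to be analysed with condition as the only factor, so any change across sessions goes into the error term; a period term would protect precision at little cost.

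*Protocol article*

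**What the plan says.** Under Study type and design: "This study will be a randomized controlled, crossover, 3-arm, clinical trial". Three conditions in three sessions give six possible orders. Under Random allocation: "The order in which the experimental sessions will be held will be randomized with the aid of the website https://www.randomizer.org". The same section adds: "The random orders generated by the program will be printed and inserted inside opaque, sequentially numbered envelopes". It does not say whether the six orders are balanced or drawn without restriction.

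Under Data analysis, for normally distributed data: "analysis of variance will be used with one source of variation (experimental situation"). The fallbacks named there, Kruskal-Wallis and Friedman, have no period term either.

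On timing, Study type and design says: "At least 4 days after the strength tests, they will carry out 3 randomized experimental sessions". Experimental sessions are then 4 to 28 days apart, with an extra familiarization session when the gap is 21 to 28 days. The intervals are to be recorded, reported and discussed. The washout is justified by an acute exercise effect of up to 2 days. The Introduction says that "the training-induced improved insulin sensitivity may be lost after as few as 4–6 days following the last training session".

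**The concern.** In a crossover each participant contributes one value per session. If insulin sensitivity shifts from session to session for reasons unrelated to the condition, a model with condition alone has two weaknesses. The shift is counted as residual variation, which widens the error term. And if one condition happens to fall earlier on average than another, part of the shift stays in that contrast.

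The article gives some reason to expect unevenness. A strenuous 8-RM test on seven exercises can fall 4 days before session 1, later gaps range from 4 to 28 days, and some participants do an extra familiarization session between periods. Reporting the intervals does not adjust for them. With 14 to 20 participants the trial depends on within-person precision, and the Weaknesses section itself relies on participants serving as their own controls.

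**Working it through.** **Plan's own figure.** Sample size gives: "inserting the parameters for a one-way ANOVA, effect size of 0.6 probability of error type alpha of 0.05". The target there is 90% power, and the section arrives at 14 individuals with actual power 0.93. With f = 0.6, three groups and 14 per group, the noncentrality is 0.6² × 42 = 15.12 on 2 and 39 df, and power is 0.928. The figure thus reproduces as 14 per group in an independent-groups ANOVA. That is a separate point; here it shows only that the planning calculation makes no allowance for period.

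**Timing.** The Strength tests section puts the 8-RM test at least 72 hours after the last familiarization session, and session 1 comes at least 4 days after the test. Session 1 is therefore at least 3 + 4 = 7 days after the last familiarization session. Only the 8-RM test itself can be as close as 4 days.

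**Chance imbalance if orders are drawn by simple randomization (an assumption).**
- P(at least one of six orders unused) = Σ(−1)^(j+1) C(6,j) ((6−j)/6)^n, which is 42% at n = 14 and 15% at n = 20.
- For two given conditions, the difference in session position is ±1 in four orders and ±2 in two, so its variance is (4×1 + 2×4)/6 = 2. The difference in mean position has mean 0 and SD √(2/14) = 0.38 sessions at n = 14, and √(2/20) = 0.32 at n = 20.
- A named pair differs by 0.5 session or more in about 20% of trials at n = 14 (13% at n = 20). At least one of the three pairs does so in about 44% (29%).
- With the six orders used as equally as possible, the SD falls to 0.13 at n = 14 and the largest possible difference is 0.21.

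**Error variance without a period term.** Assume a within-person correlation of 0.7, so the residual variance is 0.30 in units of total SD². A linear drift of d per session adds d² to the error mean square:
- d = 0.1: 0.01/0.30 = 3%
- d = 0.2: 0.04/0.30 = 13%
- d = 0.4: 0.16/0.30 = 53%

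A shift of 0.4 SD in session 1 alone adds 0.16 × (2/3)/2 = 0.053, or 18%.

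**Power.** Simulated at n = 14 with correlation 0.7 and condition means 0, 0.3 and 0.6 SD. The analysis without period is a repeated-measures ANOVA, the favourable reading of the plan. Effect, correlation and drift are assumptions. Ranges show the spread between independent simulation runs.

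| Drift | Simple randomization, no period term | Simple randomization, period term |
|---|---|---|
| none | 0.69–0.70 | 0.64–0.66 |
| 0.1 SD per session | 0.66–0.68 | 0.64–0.65 |
| 0.2 SD per session | 0.62–0.65 | 0.64–0.66 |
| 0.4 SD per session | 0.48–0.49 | 0.64–0.65 |
| 0.4 SD, session 1 only | 0.60–0.61 | 0.64–0.65 |

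Blocks of six plus a period term give about 0.68 in every row.

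**Same check at the plan's effect size.** Take f = 0.6 on the within-person SD, n = 14, simple randomization and no period term. For a total drift of 0, 0.5, 1, 1.5 and 2 within-person SDs from session 1 to session 3, power is 0.92, 0.90, 0.85, 0.75 and 0.64. Near-balanced orders plus a period term keep it at about 0.91.

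**Type I error.** Without a period term it stays at 0.05 under simple randomization, whatever the drift. If orders are balanced but period is not modelled, the test becomes conservative: null rejection is about 0.01 to 0.02 at 0.4 SD per session.

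**The case against.** The other side has a good deal of force.

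- *A reader might infer that the orders are unbalanced.* The article does not say so. It is silent on restriction, and a journal article commonly leaves that detail to the full protocol. The imbalance figures above apply only if the draw is unrestricted.
- *A reader might infer that the article makes a period effect likely*, with session 1 carrying over benefit from the familiarization block. The timing does not support that. Session 1 is at least 7 days after the last familiarization session, beyond the 4 to 6 days in the Introduction. The 8-RM test is a single bout, and 4 days exceeds the stated 2-day acute effect. Sessions 2 and 3 can also follow an exercise session by 4 days. Diet is repeated, prior activity is restricted, and premenopausal women are assessed in one menstrual phase. What remains is plausibility: the intervals are uneven, and the 4 to 6 days is given as how soon the loss can occur, not as its upper limit.
- *A reader might infer that the comparison is biased.* In expectation it is not: random order gives zero mean bias and correct type I error. A particular set of orders can shift a contrast (0.5 session × 0.4 SD = 0.2 SD), but that is chance error.
- *The gain depends on the drift assumed.* A drift of 0.4 SD per session is 0.8 SD over the trial, or 0.8/√0.30 ≈ 1.5 within-person SDs, which exceeds the assumed treatment difference. At 0.1 to 0.2 SD, the period term alone changes power by only a few points in either direction.

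None of this alters the fact that the model is stated explicitly and omits period.

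**Conclusion.** The point holds as one of precision. The plan commits to a single-factor analysis of a three-period crossover, so a period effect would inflate the error term and chance imbalance in orders would go unadjusted. The loss is negligible if drift is small and serious if it is large: about 16 power points at 0.4 SD per session, and about 3 to 5 for a 0.4 SD shift confined to session 1. With no drift, the period term costs about 1 point with balanced orders and about 4 to 5 without. These sizes rest on an assumed correlation of 0.7, an assumed effect of 0.6 SD and assumed drifts, none of which the article gives. The documents do not support a claim of systematic bias, of a likely training carry-over into session 1, or of orders known to be unbalanced. The change is cheap protection and is best made before allocation is revealed to the analyst.

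**What to change.** Replace the single-factor ANOVA under Data analysis with a within-participant primary model, for example a mixed model with condition and period as fixed effects and participant as a random effect. Fix it before the allocation codes are opened. Under Random allocation, state whether the six orders are balanced. If they are unrestricted, generate the remaining envelopes in permuted blocks of six, each block holding every order once, and fit period for everyone, including those already randomized. Neither 14 nor 20 is a multiple of six, so balance will be close rather than exact. Do not balance the orders without adding the period term: the unadjusted test then becomes conservative, and power is not recovered.

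The cost is one model term using 2 error degrees of freedom, the small loss of power given above if there is no drift, and reprinting the unused envelopes. The last orders in a block can be guessed by someone who knows the block size, so keep it from those who enrol. No extra participants, sessions or measurements are needed.
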